### Inclusion and exclusion criteria (Aim 1)

The inclusion criterion is continuous fee-for-service Medicare enrollment for at least 12 months prior to AF diagnosis or matched index date (July 1 of inclusion year) for controls and continuous enrollment in fee-for-service (FFS) Medicare after AF diagnosis/index date for at least 12 months or until death if death occurred before 12 months of continuous enrollment.

Patients with prevalent AF will be identified as follows:ICD-9-CM code 427.31 or ICD-10-CM code I48 in 2 outpatient claims or 1 inpatient claim within 365 days, in any diagnosis position of the claim [16–18]. The index date will be the date of the first qualifying inpatient claim or second qualifying outpatient claim. Patients will be required to have 12 months of FFS claims without an AF diagnosis prior to the index AF claims based on inclusion criteria.

Exclusion criteria are:

patients with any claim for CRAO in the 12 months prior to AF diagnosis or index date for controls (July 1 of potential inclusion year).

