### Inclusion and exclusion criteria (Aim 2)

Inclusion criteria are fee-for-service Medicare enrollment for at least 12 consecutive month and 12 months FFS with Part A, B, and D enrollment following the index date for at least 12 months or until death, and presence of atrial fibrillation as defined in the exposure section. The index date for patients exposed to anticoagulation will be the date of the first anticoagulant prescription drug claim occurring after the diagnosis of AF. For potential controls, only patients with no exposure to anticoagulation throughout the study period would be eligible to avoid selecting controls who start an anticoagulant during the follow-up period. For controls, inclusion and exclusion criteria will be examined for each year after AF diagnosis, and the midpoint of one random year will be selected as the index date for each control patient.

Exclusion criteria include:

Patients with any claim for CRAO in the 12 months prior to AF diagnosis or index date for controls;Patients who die within first 12 months of enrollment;Patients taking therapeutic-dose heparin, enoxaparin, dalteparin, fondaparinux, or betrixaban.

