1) We will repeat the primary analysis, classifying CRAO based on the presence of the ICD codes in any diagnosis position rather than the primary diagnosis position.2) We will perform a sensitivity analysis for any retinal artery occlusion, using ICD-9-CM codes 362.3, 362.30, 362.31, 362.32, 362.33 and ICD-10-CM codes H34.9, H34.233, H34.1x, H34.0x, H34.12, H34.13, H34.23x, H34.21x) [31].i) We will perform a secondary analysis of patients with CRAO who later developed atrial fibrillation, to assess the hypothesis that clinically undetected paroxysmal AF may be associated with CRAO.j) Table shell for Aim 1 regression results are provided in Tables 6 and 7. The primary outcome is underlined.k) To address confounding resulting from patients potentially receiving a competing therapy (left atrial appendage occlusion, a procedural alternative to long-term oral anticoagulation), we will exclude patients with ICD-9-CM procedure code 37.90 or ICD-10-CM 02L73DK either in the follow-up period or in the ascertainment period.

**Table 6 pone.0296251.t006:** Crude and adjusted rates of CRAO in patients with and without atrial fibrillation.

	AF		No AF		AF	No AF	Rate Difference (95% CI)	aHR (95% CI)
	Patients with event	Rate per 1000 Or 100,000 Person-years	Patients with event	Rate per 1000 Or 100,000 Person-years	Adjusted rate per 1,000 person-years	Adjusted rate per 1,000 person-years		
CRAO (Overlap weighted)								
CRAO (primary Dx)								
Any RAO								
Ischemic stroke								
UTI								

**Table 7 pone.0296251.t007:** Hazard ratios for atrial fibrillation vs. no atrial fibrillation for Aim 1.

Outcome	Unadjusted Model	Adjusted Model†
CRAO (Overlap weighted)	HR (95% CI)	aHR (95% CI)
CRAO (primary dx)	HR (95% CI)	aHR (95% CI)
Any RAO	HR (95% CI)	aHR (95% CI)
CRAO (any dx position)	HR (95% CI)	aHR (95% CI)
Ischemic Stroke	HR (95% CI)	aHR (95% CI)
UTI	HR (95% CI)	aHR (95% CI)

^†^This column reflects the results of a model that incorporates overlap weighting using propensity scores re-estimated after our first stage matching procedure.

We will report a figure showing the adjusted cumulative incidence of CRAO according to AF vs. No AF groups using an overlap-weighted cumulative incidence function.

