### Limitations

The principal limitation of this study is its observational, retrospective nature. Unfortunately, the incidence of CRAO is low, and evaluating the effect of anticoagulation on primary or recurrent CRAO risk is likely to be infeasible given the massive study sizes that would be required to detect an effect. While our target trial emulation methodology, including careful selection of index date and control patients and our use of overlap weighting methodology, can help to answer this question to its best extent using real-world data, the potential for residual confounding is still present in any observational data source. Additional limitations include the use of Medicare data, which has several intrinsic limitations, including having a limited number of beneficiaries under the age of 65, lacking access to clinical data not captured in structured claims, and limited ascertainment of key information on demographic identity, including gender identity and race/ethnicity. Another limitation in any non-controlled study of anticoagulation is the fact that the antithrombotic effect of anticoagulation varies according to patient adherence, especially for patients taking Warfarin. The use of Medicare Part D data has one major advantage in that it captures medication fills, not medication prescriptions, therefore giving a better surrogate of patient adherence, although some patients may not take medications that they nonetheless fill, recognizing that generalizability may be limited to Part D enrollees. Treating exposure to anticoagulation as a time-varying covariate will also help to capture more precisely the effect that therapeutic anticoagulation has on CRAO risk. Furthermore, our use of both positive and negative control endpoints in this analysis should help to interpret our eventual findings: existing evidence from randomized controlled trials has shown that use of anticoagulation is highly effective in preventing embolic stroke due to atrial fibrillation, and is associated with an increased risk of intracranial hemorrhage; if we replicate these results in our study design, it gives increased confidence that our results concerning CRAO may be valid. Finally, some patients with contraindication to oral anticoagulation may receive alternative management strategies that can decrease their ischemic stroke risk, such as receipt of a left atrial appendage occlusion device. We address this limitation through a sensitivity analysis excluding any patient who receives a LAAO during the study follow-up period or with a diagnostic code indicating the placement of an LAAO in the comorbidity ascertainment window.

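### Aim 2 admits patients who die within 12 months after index but also excludes early deaths; as the time origin is undefined, the exclusion is either redundant or selects on post-index survival

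*Protocol article*

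**What the plan says.** In the Protocol article, Inclusion and exclusion criteria (Aim 2), the inclusion rule requires "12 months FFS with Part A, B, and D enrollment following the index date for at least 12 months or until death". The exclusion list in the same section removes "Patients who die within first 12 months of enrollment". For treated patients the index date is "the date of the first anticoagulant prescription drug claim occurring after the diagnosis of AF". For controls it is the midpoint of one randomly chosen eligible year after AF diagnosis.

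Aim 1 has a similar enrollment rule, "continuous enrollment in fee-for-service (FFS) Medicare after AF diagnosis/index date for at least 12 months or until death", with the same allowance for death ("or until death if death occurred before 12 months of continuous enrollment"). Its only listed exclusion is a prior CRAO claim. It has no early-death exclusion.

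Under Analytical cohort, and again under Regression modeling (aim 1) item b, patients are censored at death, at the end of fee-for-service (FFS) enrollment, or at the end of the data. Regression modeling (aim 2) item a and Limitations describe the design as a target trial emulation.

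On left atrial appendage occlusion (LAAO), Regression modeling (aim 1) item k excludes patients with a procedure code "either in the follow-up period or in the ascertainment period" and does not call this a sensitivity analysis. Limitations describes a "sensitivity analysis excluding any patient who receives a LAAO during the study follow-up period".

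**The concern.** A patient who dies in month 5 after index meets the Aim 2 inclusion rule and may or may not meet the exclusion, depending on what *enrollment* is taken to mean. Two programmers could build different Aim 2 cohorts from the same text.

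If the exclusion runs from index, the matter goes beyond wording. A trial cannot enroll on future survival, so an emulation should not either. Every retained patient would have a guaranteed first year, and events before an early death would vanish. The loss is unequal if first-year mortality differs between anticoagulated and untreated patients.

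The control endpoints are also exposed. Limitations relies on reproducing the known effects of anticoagulation on embolic stroke and intracranial hemorrhage to support the CRAO result. Events of these types that are followed by death in the first year are the ones the rule would remove.

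**Working it through.** **The two readings side by side**

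- *Medicare enrollment before index.* Aim 2 already asks for at least 12 consecutive months of FFS enrollment. It does not say outright that these precede index, but Aim 1 does, and the comorbidity look-back is 12 months. A patient with 12 prior months cannot have died in them, so the exclusion removes nobody.
- *Enrollment after index.* The inclusion rule keeps a death before month 12 and the exclusion drops it. The criteria contradict each other, and entry depends on 12-month survival.

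Only the second reading gives the exclusion any effect.

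**Possible size under the second reading**

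The protocol has no figure to reproduce here: it gives no Aim 2 sample size and no mortality by anticoagulation status. What follows is an illustration.

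Inputs:
- CRAO rate of 22 per 100,000 per year, the exposed-group rate under Sample size calculation. It cancels in the ratios.
- Assumed: 30% of each group is frail, with 3 times the CRAO hazard and 3 times the death hazard, not captured by the weights.
- Assumed: true hazard ratio for anticoagulation 1.00.
- Assumed: first-year mortality d of 10% treated and 10, 15, 20 or 30% untreated.

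Formulas, per patient, over year 1:
- Non-frail CRAO rate: b = 22 / (0.7 + 0.3 × 3) = 13.75 per 100,000.
- Non-frail death hazard h solves 0.7·e^(−h) + 0.3·e^(−3h) = 1 − d.
- Deaths kept: events = 0.7·b·(1 − e^(−h))/h + 0.3·3b·(1 − e^(−3h))/(3h). Person-years are the same sum without b and 3b.
- Deaths excluded: events = 0.7·b·e^(−h) + 0.3·3b·e^(−3h). Person-years = 1 − d.

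Worked case, 10% treated and 20% untreated (events per 100,000 patients, rates per 100,000 person-years):
- Treated, h = 0.0670: kept 20.52 / 0.9488 = 21.63; excluded 19.12 / 0.90 = 21.25; events lost 1 − 19.12/20.52 = 7%.
- Untreated, h = 0.1447: kept 19.00 / 0.8951 = 21.23; excluded 16.34 / 0.80 = 20.43; events lost 1 − 16.34/19.00 = 14%.
- Rate ratio: kept 21.63/21.23 = 1.02; excluded 21.25/20.43 = 1.04.

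| Untreated mortality (treated 10%) | Rate ratio, deaths kept | Rate ratio, deaths excluded | First-year CRAO lost, untreated / treated |
|---|---|---|---|
| 10% | 1.00 | 1.00 | 7% / 7% |
| 15% | 1.01 | 1.02 | 10% / 7% |
| 20% | 1.02 | 1.04 | 14% / 7% |
| 30% | 1.04 | 1.09 | 22% / 7% |

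With deaths kept, the ratio drifts from 1.00 because frail patients leave the untreated group faster. Excluding deaths adds at most about 0.05 (1.09 − 1.04). In this model the bias is nil when mortality is equal and grows with the gap.

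The model leaves out one feature. A control who dies can still enter through an earlier eligible year, whereas a treated patient has a single fixed index. The rule could therefore act differently by group even at equal mortality.

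**The case against.** The Aim 2 section uses the term index date where it means index, and the exclusion does not use it. That favors the harmless reading, under which nothing is selected and one line is superfluous. This stands as a reason not to assert post-index selection as fact. It does not remove the need to define the term.

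A reader might infer more than the protocol supports in four places.

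- *That the plan follows patients until death and then excludes the deaths.* The phrase in the inclusion rule is an allowance within an enrollment requirement. Follow-up to death comes from the censoring text.
- *That LAAO makes Aim 2 eligibility depend on later treatment.* Aim 2 lists no LAAO criterion. Item k belongs to Aim 1, Limitations calls it a sensitivity analysis, and it reaches Aim 2 only because item e repeats the Aim 1 sensitivity analyses. It does not alter a primary estimate if it is only that. Dependence on future treatment comes from the control rule, "only patients with no exposure to anticoagulation throughout the study period would be eligible", which is a separate matter.
- *That the bias is large.* Suppose 20% untreated and 10% treated mortality, decedents contributing half a year, and a 3-fold event rate in decedents. The untreated rate is (0.8 + 0.1 × 3)/0.9 = 1.22 and the treated rate (0.9 + 0.05 × 3)/0.95 = 1.11, a ratio of 0.90. Deletion makes it 1.00 and loses 0.3/1.1 = 27% and 0.15/1.05 = 14% of events. But rates within survivors and within decedents are the same in both groups, and no true effect is specified. The example shows movement, not movement away from the truth.
- *That an endpoint with 30-50% one-year fatality (assumed) loses that share of first-year events.* Death must fall within 12 months of index, not of the event. With events uniform over year 1 and those deaths uniform over the following year, half qualify: 15-25%. The 30-50% is an upper bound, reached only if those deaths are immediate.

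Two further objections carry weight. Overlap weighting on age, comorbidities and bleeding history should narrow any mortality gap. And a post-index enrollment requirement is compatible with later censoring, so it is a weaker design choice rather than a contradiction.

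**Conclusion.** The Aim 2 inclusion and exclusion criteria need reconciling. On the only reading under which the early-death exclusion does anything, it contradicts the inclusion rule, makes entry depend on 12-month survival after time zero, and removes first-year events in patients who die. On the other reading it is redundant. Either way it serves no purpose, because death is already a censoring event.

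The size of any bias cannot be determined from the protocol. In the illustration the first-year rate ratio, truly 1.00, is 1.00-1.04 with deaths kept and 1.00-1.09 with deaths excluded. That range rests on the assumed mortality, frailty share and 3-fold hazards, and it covers year 1 only, whereas follow-up runs longer.

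The LAAO point is secondary. The label differs between item k and Limitations, and excluding on a procedure during follow-up is selection on the future even in a sensitivity analysis.

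**What to change.** - Delete the early-death exclusion from Aim 2. Start follow-up at index and rely on the existing censoring at death, end of FFS enrollment and end of data, adding end of Part D enrollment for Aim 2.
- Preferably also drop the 12-month post-index enrollment requirement, which selects on future enrollment and is not needed given that censoring.
- State once that the LAAO exclusion is a sensitivity analysis, if that is what is meant. In it, exclude only patients with LAAO on or before index and censor at a later LAAO. Such censoring can itself be informative, so report it with that caveat.

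The cost is a few lines of wording and simpler cohort code. Some patients will contribute short follow-up. The change should be settled before the Aim 2 cohort is built.

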### Exposure

The primary exposure of interest is prevalent atrial fibrillation/atrial flutter. Atrial fibrillation/atrial flutter will be defined through ICD-9-CM 427.13 or ICD-10-CM code I48 in 2 outpatient claims or one inpatient claim within 365 days [16–18]. Episodes of atrial fibrillation within 1 month of inpatient surgery will be excluded to avoid including patients with isolated post-operative atrial fibrillation [19].

The secondary exposure of interest (among patients with atrial fibrillation) is exposure to anticoagulation. For our secondary analysis (Objective 2), we will utilize Medicare Part D prescription drug claims to identify patients taking a direct acting oral anticoagulant (DOAC) or warfarin.

A list of search terms to identify anticoagulant drugs will be utilized as per Table 1, below:

**Table 1 pone.0296251.t001:** Drug lookup queries for anticoagulant exposure.

Drug Name	
Warfarin	Part D claim for generic drug name like ‘%WARFARIN%’, summarized per month (90-day fills will be imputed to monthly indicators)
Apixaban	Part D claim for generic drug name like ‘%APIXABAN%’, summarized per month (90-day fills will be imputed to monthly indicators)
Dabigatran	Part D claim for generic drug name like ‘%DABIGATRAN%’, summarized per month (90-day fills will be imputed to monthly indicators)
Edoxaban	Part D claim for generic drug name like ‘%EDOXABAN%’, summarized per month (90-day fills will be imputed to monthly indicators)
Rivaroxaban	Part D claim for generic drug name like ‘%RIVAROXABAN%’, summarized per month (90-day fills will be imputed to monthly indicators)

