**Charlson Comorbidity Variables**			
Myocardial Infarction	410.*, 412.*	I21.*, I22.*, I25.2*	Quan, 2005 [20]
Congestive Heart Failure	398.91, 402.01, 402.11, 402.91, 404.01, 404.03, 404.11, 404.13, 404.91, 404.93, 425.4, 425.5, 425.7, 425.8, 425.9, 428*	I09.81, I11.0*, I13.0*, I13.2*, I42.0*, I42.5*-I42.9*, I43.*, I50.*	Quan, 2005 [20]
Peripheral Vascular Disease	093.0*, 437.3*, 440.*, 441.*, 443.1*, 443.2*, 443.8*, 443.9*, 447.1*, 557.1*, 557.9*, V43.4*	A52.01*, E08.51, E08.52, E09.51, E09.52, E10.51, E10.52, E11.51, E11.52, E13.51, E13.52, I67.0*, I67.1*, I70.*, I71.*, I73.1*, I73.8*, I73.9*, I77.7*, I79.*, K55.1*, K55.8*, K55.9*, Z958.2*	Quan, 2005 [20]
Cerebrovascular Disease†††	430*, 431*, 432.*, 433.*, 434.*, 435.*, 436*, 437.*, 438.*	G45.0, G45.1, G45.2, G45.4, G45.8, G45.9, G46.*, I60.*-I63.*, I65.*-I66.*, I67.1*, I67.2*, I67.4*, I67.5*, I67.6*-I67.7*, I67.81, I67.82, I67.84, I67.89, I67.9*, I68.*-I69.*	Quan, 2005[20]
Dementia	290.*, 294.1*, 331.2*	F01.*, F02.*, F03.9*, G31.1*	Quan, 2005 [20]
Chronic Pulmonary Disease	416.8*, 416.9*, 490*, 491.*, 492.*, 493.*, 494.*, 495.*, 496*, 500*, 501*, 502*, 503*, 504*, 505*, 506.4*, 508.1*, 508.8*	I27.2*, I27.81, I27.89, I27.9*, J40.*-J44.*, J45.2*-J45.5*, J45.90, J45.99, J47.*, J60.*, J61.*-J67, J68.4*, J70.1*, J70.2*, J70.3*, J70.4*, J70.8*	Quan, 2005 [20]
Connective Tissue Disease	446.5*, 710.0*, 710.1*, 710.2*, 710.3*, 710.4*, 714.0*, 714.1*, 714.2*, 714.8*, 725*	M05.*, M06.*, M31.5*, M31.6*, M32.*-M34.*, M35.0*, M35.3*, M36.0*	Quan, 2005 [20]
Peptic Ulcer Disease	531.*, 532.*, 533.*, 534.*	K25.*-K28.*	Quan, 2005 [20]
Mild Liver Disease	070.22, 070.23, 070.32, 070.33, 070.44, 070.54, 070.6*, 070.9*, 570*, 571.*, 573.3*, 573.4*, 573.8*, 573.9*, V42.7*	B17.9*, B18.0*-B18.2*, B19.0*, B19.9*, K70.0, K70.1*, K70.2, K70.3*, K70.40, K70.9, K71.*, K72.00, K73.*, K74.0*, K74.1*-K74.6*, K75.2*-K75.4*, K75.8*, K75.9*, K76.0*-K76.5*, K76.89, K76.9*, K77.*, Z48.23, Z94.4*	Quan, 2005 [20]
Diabetes without complications	250.0*, 250.1*, 250.2*, 250.3*, 250.8*, 250.9*	E10.1*, E10.618, E10.62*, E10.63, E10.64, E10.65, E10.69, E10.8*, E10.9*, E11.0*, E11.1*, E11.618, E11.62-E11.65, E11.69, E11.8*, E11.9*, E13.00, E13.01, E13.10, E13.11, E13.618, E13.62-E13.65, E13.69, E13.8*, E13.9*	Quan, 2005 [20]
Diabetes with complication	250.4*, 250.5*, 250.6*, 250.7*	E10.2*-E10.5*, E10.610, E11.2*-E11.5*, E11.610, E13.2*-E13.5*, E13.610	Quan, 2005 [20]

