^†††^ The Quan, 2005 algorithm uses ICD-9-CM 362.34 (transient retinal artery occlusion) and ICD-10-CM H34.0 (transient retinal artery occlusion) as part of the algorithm for identifying cerebrovascular disease; we have removed these specific codes from our comorbidity list due to the possibility that CRAO may have been miscoded as 362.34 or H34.0 due to similar clinical presentation.

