#### Regression modeling (aim 1)

a) The study index date will be the date of the first AF claim in the study and July 1 in the first year of inclusion in the analytic cohort for controls for the purposes of our survival analysis.b) We will describe cumulative incidence of CRAO over time with the overlap-weighted cumulative incidence function and presented graphically for patients with and without atrial fibrillation. Next, a weighted, unadjusted cause-specific hazard model will be fit with AF as the univariable predictor and CRAO as the event of interest, with patients censored at death, at end of data availability, or at end of fee-for-service Medicare enrollment.c) Then, a weighted cause-specific hazard model, clustered by state, and adjusting for age, sex, race, cardiovascular comorbidities will be fitted. Directly adjusted cumulative incidence curves for AF and control patients will be created with adjustment for all model covariates [28].d) We will test the proportional hazards assumption for all models.e) Our primary analytical model will be an overlap-weighted model with propensity scores derived from the adjustment covariates previously described as predictors for the presence of atrial fibrillation. We will report our results with sequential adjustment to produce the fully-adjusted, weighted model. We employ this sequential adjustment strategy to provide insight as to sources of measured confounding.f) We will evaluate **positive control endpoints**. Our positive control endpoints will be any ischemic stroke (defined by ICD-9-CM 434.0, 434.00, 434.10, 434.11, 434.9, 434.90, 434.91, 436/ ICD-10-CM I66.09, I66.19, I66.29, I66.9, I63.40, I63.50, I67.89 in the primary diagnosis position in a hospitalization or ED visit) [29]. We will utilize the same modeling strategy as used for the primary outcome.g) We will evaluate **negative control (falsification) endpoints**. Our negative control endpoint will be hospitalized/ED urinary tract infection (including renal abscess and pyelonephritis) (ICD-9-CM 590.1, 590.11 590.2, 590.8 or 599.0/ ICD-10-CM N15.1, N39.0, N10). We will utilize the same modeling strategy as used for the primary outcome [30].h) We will perform several sensitivity analyses for outcome ascertainment.

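### The AF code differs between the Aim 1 criteria (427.31) and the Exposure section that Aim 2 relies on (427.13), and the any-RAO list changes meaning at the ICD-9/ICD-10 switch

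*Protocol article*

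**What the plan says.** **AF.** The Inclusion and exclusion criteria (Aim 1) identify AF by "ICD-9-CM code 427.31 or ICD-10-CM code I48 in 2 outpatient claims or 1 inpatient claim within 365 days". The Exposure section says "Atrial fibrillation/atrial flutter will be defined through ICD-9-CM 427.13 or ICD-10-CM code I48", with the same claim-count rule and the same three references. The Inclusion and exclusion criteria (Aim 2) require "presence of atrial fibrillation as defined in the exposure section", so Aim 2 takes the 427.13 version.

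**Any RAO.** Regression modeling (aim 1), item h, defines this sensitivity endpoint by "ICD-9-CM codes 362.3, 362.30, 362.31, 362.32, 362.33 and ICD-10-CM codes H34.9, H34.233, H34.1x, H34.0x, H34.12, H34.13, H34.23x, H34.21x". A footnote to Table 2 removes two codes from the cerebrovascular comorbidity group and says what each means: "ICD-9-CM 362.34 (transient retinal artery occlusion) and ICD-10-CM H34.0 (transient retinal artery occlusion"). It adds that CRAO may have been miscoded to either one.

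**Ischemic stroke (positive control).** Item f of the same section lists "ICD-9-CM 434.0, 434.00, 434.10, 434.11, 434.9, 434.90, 434.91, 436/ ICD-10-CM I66.09, I66.19, I66.29, I66.9, I63.40, I63.50, I67.89". The cerebrovascular row of Table 2 uses whole ICD-10 families, among them "I60.*-I63.*, I65.*-I66".

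**The concern.** These lists are operative rules. They decide who is exposed and what counts as an event, and the study window crosses the coding switch.

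In Aim 2, the date of AF diagnosis drives three things:

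- who is eligible;
- the index date, which for treated patients is the first anticoagulant fill after diagnosis and for untreated patients is the middle of a randomly chosen later year;
- time since first AF claim, which is a propensity-score variable.

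A code that fails to find AF before the switch disturbs all three. Patients with AF claims only before the switch would be lost. Patients with claims on both sides would appear newly diagnosed at their first qualifying I48 claims, so a fill made years into treatment could be taken as the first.

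For any RAO, the endpoint would be one event before the switch and a broader one after it. A difference from the primary result could then reflect coding era rather than outcome definition. The analysis also carries into Aim 2, which repeats the Aim 1 sensitivity analyses.

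**Working it through.** No figure in the plan rests on these lists: the sample-size statement uses assumed event rates and a hazard ratio. The check is a side-by-side comparison plus one calendar calculation.

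**1. AF code.**

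| Place | ICD-9-CM | ICD-10-CM | Label |
|---|---|---|---|
| Aim 1 criteria | 427.31 | I48 | AF |
| Exposure (used by Aim 2) | 427.13 | I48 | AF/atrial flutter |

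The sets {427.31, I48} and {427.13, I48} share only I48. Everything else in the rule matches, so one algorithm is given with two different ICD-9 codes.

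**2. Any RAO.**

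| Event, as the Table 2 footnote describes it | ICD-9 list | ICD-10 list |
|---|---|---|
| Transient retinal artery occlusion | 362.34: absent | H34.0x: present |

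Transient events count after the switch and not before it.

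**3. Flutter (conditional).** The Exposure section declares AF and flutter together. Its ICD-9 side is one five-digit code, its ICD-10 side is the whole I48 category, and no separate ICD-9 flutter code appears anywhere in the article. If the single code does not include flutter, flutter-only patients are captured only after the switch. Before it they could fall among the remaining beneficiaries from whom the Analytical cohort section draws controls. The article gives no code titles, so this needs the code book.

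**4. Stroke (conditional).** The ICD-9 list runs 434.00, 434.10, 434.11, 434.90, 434.91, so 434.01 is the gap. From the I63 family the ICD-10 list takes only I63.40 and I63.50, while Table 2 uses the entire family. The breadth of the endpoint appears to change at the switch. What each code covers again needs the code book.

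**5. Calendar share.** The window is taken as January 2000 to December 2020 (Design and setting). The switch is taken as the end of September 2015, because the date printed in the Outcome section, September 31, does not exist.

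- ICD-9 months: 15 × 12 + 9 = 189
- All months: 21 × 12 = 252
- ICD-9 share: 189 / 252 = 0.75
- ICD-10 share: (252 − 189) / 252 = 63 / 252 = 0.25

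**The case against.** The AF discrepancy looks like two transposed digits. Both statements describe the same algorithm, and the fuller one, with diagnosis position and index date, has 427.31. The Sample size calculation reports 818,940 AF patients from a 2000–2015 query, almost all ICD-9 era, so a working query evidently existed, and a run on the wrong code would probably fail visibly. This bears on how likely the error is to reach the data; it does not reconcile the text. Under the Data management plan, those drafting the manuscript will not have access to the raw data or the analytical environment, so the written code list is the safeguard.

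For any RAO, 362.3 could be read as a prefix that takes in 362.34. The list also names 362.30 to 362.33 one by one and marks ICD-10 wildcards with an x, so this is the less natural reading. Reading 434.0 as a prefix would close the 434.01 gap in the same way, but 434.00 is then redundant. The narrow stroke list carries a citation that might justify it, which is one reason that part stays conditional.

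Four stronger readings are tempting, and the article does not support them:

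- **That 75% of Aim 2 is affected.** The 75% is a share of calendar time. Aim 2 is limited to Part D enrollees, and its person-time by era is not given.
- **That a definite fraction of controls is really flutter.** The article gives no flutter share, and a share of AF/flutter patients would not be a share of matched controls anyway.
- **That the stroke control misses most infarctions after the switch.** This needs code meanings and frequencies that the article does not give. Stroke is also not the only benchmark: the Limitations name intracranial hemorrhage too, and rely on negative controls as well.
- **That the primary result is compromised by its outcome codes.** The primary pair, 362.31 and H34.1x, is not touched by any of this.

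**Conclusion.** Two defects are established by the article's own text. The AF code in the Exposure section contradicts the Aim 1 criteria and governs Aim 2. The any-RAO endpoint includes transient occlusion in one coding era only. Both would matter if the lists were programmed as written: the first for Aim 2 eligibility, index dates and time since first AF claim, the second for one sensitivity analysis in each aim.

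The flutter and stroke asymmetries are secondary. The difference in breadth is visible on the page, but its clinical content depends on the ICD code books and, for stroke, on the cited algorithm.

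The ICD-9 era is 189 of 252 months (75%) of the calendar window, assuming full calendar years and a switch at the end of September 2015. The effect on Aim 2 patients, person-time or hazard ratios cannot be quantified from the article. The sample-size figures do not change.

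**What to change.** - **AF:** state one identical code set in the Aim 1 criteria and the Exposure section, with 427.31 in place of 427.13. Then either make the ICD-9 side match I48 on flutter or restrict both eras to AF, and use the same label in both places.
- **Any RAO:** add 362.34 or drop H34.0x, so that transient occlusion is in or out in both eras.
- **Ischemic stroke:** align the two lists so that they capture the same event, using the I63 family as in Table 2 unless the cited algorithm justifies the narrow list. Resolve 434.01 at the same time.
- **Switch date:** correct the date in the Outcome section.

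The cost is revised code lists and a check against the code books. Because the Status and timeline section starts preliminary cohort creation at submission of the protocol, any cohort already built from the printed lists would have to be re-run. No change to the design or sample size is needed.
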